## Abstract

**Background:**

Minimally invasive thoracic surgery (MITS) has been shown to reduce postoperative pain and contribute to better postoperative quality of life as compared to open thoracic surgery (Bendixen et al., Lancet Oncol 17:836–44, 2016). However, it still causes significant post-operative pain. Regional anaesthesia techniques including fascial plane blocks such as the erector spinae plane block (ESP) have been shown to contribute to post-operative pain control after MITS (Finnerty et al., Br J Anaesth 125:802–10, 2020). Case reports relating to ESP catheters have described improved quality of pain relief using programmed intermittent boluses (PIB) instead of continuous infusion (Bendixen et al., Lancet Oncol 17:836–44, 2016). It is suggested that larger, repeated bolus dose may provide superior pain relief, possibly because of improved spread of the local anaesthetic medications (Ilfeld and Gabriel, Reg Anesth Pain Med 44:285–86, 2019). Evidence for improved spread of local anaesthetic may be found in one study which demonstrated that PIB increased the spread of local anaesthetic medication compared to continuous infusions for continuous paravertebral blocks, which are another type of regional anaesthesia technique for the chest wall (Hida et al., Reg Anesth Pain Med 44:326–32, 2019). Similarly, regarding labour epidural analgesia, the weight of evidence is in favour of PIB providing better pain relief compared with continuous infusion (Onuoha, Anesthesiol Clin 35:1–14, 2017).

Since fascial plane blocks, such as ESP, rely on the spread of local anaesthetic medication between muscle layers of the chest wall, intermittent boluses may be particularly useful for this group of blocks. However, until recently, pumps capable of providing automated boluses in addition to patient-controlled boluses were not widely available. To best of our knowledge, there are no randomised controlled trials comparing continuous infusion versus intermittent bolus strategies for erector spinae plane block for MITS in terms of patient centred outcomes such as quality of recovery.

**Methods:**

This trial will be a prospective, double-blinded, randomised controlled superiority trial. A total of 60 eligible patients will be randomly assigned to receive an intermittent bolus regime of local anaesthetic vs a continuous infusion of local anaesthetic. The medication will be delivered via an ultrasound-guided erector spinae plane block catheter which will be inserted by an anaesthesiologist while the patient is under general anaesthetic before their MITS surgery begins. The primary outcome being measured is the Quality of Recovery (QoR-15) score between the two groups 24 h after surgery. Secondary outcomes include respiratory testing of maximal inspiratory volume measured with a calibrated incentive spirometer, area under the curve for Verbal Rating Score for pain at rest and on deep inspiration versus time over 48 h, total opioid consumption over 48 h, QoR-15 score at 48 h and time to first mobilisation.

**Discussion:**

Despite surgical advancements in thoracic surgery, severe acute post-operative pain following MITS is still prevalent. This study will provide new knowledge and possible recommendations about the efficacy of programmed intermittent bolus regimen of local anaesthetic vs a continuous infusion of local anaesthetic via an ultrasound-guided erector spinae plane catheter for patients undergoing MITS.

**Trial registration:**

This trial was pre-registered on ClinicalTrials.gov Identifier: NCT05181371. Registered on 6 January 2022. All item from the World Health Organization Trial Registration Data set have been included.

**Supplementary Information:**

The online version contains supplementary material available at 10.1186/s13063-022-06726-7.

## Administrative information

Note: the numbers in curly brackets in this protocol refer to SPIRIT checklist item numbers. The order of the items has been modified to group similar items (see http://www.equator-network.org/reporting-guidelines/spirit-2013-statement-defining-standard-protocol-items-for-clinical-trials/).

## Introduction

### Background and rationale {6a}

Minimally invasive thoracic surgery (MITS) is a surgical method used to perform lung surgery through small surgical incisions between the ribs and includes both video-assisted thoracic surgery (VATS) and robotic assisted thoracic surgery (RATS) [1, 2]. MITS has increased to almost half of all thoracic surgery in the past decade [3]. When compared to thoracotomy, MITS is associated with less pain, better shoulder function, earlier mobilisation, shorter LOS, better preservation of pulmonary function and better quality of life [3, 4]. Despite surgical advancements in thoracic surgery, severe acute post-operative pain following MITS is still prevalent [5].

In the past 5 years, the erector spinae plane (ESP) block has emerged as a novel regional anaesthesia procedure which has had some promising early results in attenuating this severe acute pain of MITS. In a recent RCT among MITS patients, single shot ESP block improved QoR-15 and reduced overall complications at 24 h compared with single-shot serratus anterior plane block [6]. Furthermore, our research group recently completed a randomised controlled trial comparing the efficacy of ESP catheters vs the gold standard paravertebral catheters for patients undergoing MITS and is currently under peer review [7].

Evidence for the improved spread of local anaesthetic with the use of programmed intermittent bolus techniques [8] have been described in studies of paravertebral blocks, which demonstrated that automated boluses increased the number of affected dermatomal levels compared to continuous infusions and could benefit patients requiring a wider extent of anaesthesia [9, 10]. Similarly, regarding labour epidural analgesia, the weight of evidence is in favour of programmed intermittent boluses [11]. Studies in this patient population have demonstrated the benefits of the programmed intermittent epidural bolus technique, including the use of less local anaesthetic and opioids, the occurrence of less breakthrough pain, improved patient satisfaction and potentially a lower incidence of both motor block and instrumental vaginal delivery [12, 13].

This study will provide new knowledge and possible recommendations about the efficacy of programmed intermittent bolus regimen of local anaesthetic vs a continuous infusion of local anaesthetic via an ultrasound-guided erector spinae plane catheter for patients undergoing MITS.

### Objectives {7}

Our main aim and corresponding hypotheses are outlined below:

We aim to complete a prospective, double blinded, factorial design, randomised controlled, superiority trial to test the hypothesis that programmed intermittent bolus techniques, as a maintenance mode for analgesia via erector spinae plane catheters, may provide better outcomes over traditional continuous infusion techniques, in terms of early recovery (QoR-15) at 24 h after MITS surgery.

### Trial design {8}

We outline a research protocol for a double-blind, randomised controlled, superiority trial. Patients who enrol to this clinical trial will be randomly and equally (1:1) allocated into one of two intervention groups: programmed intermittent bolus (PIB) regime of local anaesthetic vs a continuous infusion (CI) of local anaesthetic via an ultrasound-guided erector spinae plane block catheter. Both groups will receive the same standardised pain relief protocol both during and after their surgery. Figure 1 illustrates the study flow chart. Recruitment commenced on June 2022, and it is expected to take between 9 and 12 months to complete.

**Fig. 1 Fig1:**
[figure not shown]
Study flow chart

## Methods: participants, interventions, and outcomes

### Study setting {9}

Ethical approval (Institutional Review Board; reference number 1/378/2292) has been granted for Mater Misericordiae University Hospital (MMUH), Dublin, Ireland, and recruitment has begun. In addition, we are currently seeking ethical approval for a second clinical site (St. James’s Hospital, Dublin, Ireland).

### Eligibility criteria {10}

The eligibility criteria for patients to enrol in this study are as follows.

Inclusion criteriaMale and female aged > 18Able to provide written informed consentASA grade I – VMITS surgeryWeight > 55kg

Exclusion criteriaAbsence of or inability to give informed consentPre-existing infection at block siteSevere coagulopathyAllergy to local anaesthesia (or another contraindication to block performance)Previous history of opiate abusePre-existing chronic pain conditionPre-existing dementia (due to need to co-operate in completing QoR-15 score day after surgeryPostoperative admission to ICU for continued ventilationBMI > 40 kg/m^2^

### Who will take informed consent? {26a}

Potential participants for this trial will be identified by a member of the surgical, anaesthetic or research team. These patient’s electronic medical records will be analysed by a member of the research team to determine if they are suitable candidates for this trial, i.e. if they meet the inclusion criteria and have no reason for exclusion.

Suitable patients will be approached the evening before surgery where possible. Alternatively, patients will be approached on the ward on the morning of surgery and their suitability to participate in the trial will be confirmed. The purpose of the trial including benefits and risks, and method of follow up will be explained to patients. A comprehensive and instructive information leaflet will be given to each patient, and they will be provided an adequate amount of time to study it (minimum 10 min). Patients will be informed that their participation in the study is entirely voluntary and they will have the opportunity to withdraw from the study at any time, and this will not affect the quality of care they receive. Finally, a member of the research team will obtain informed written consent from the participant.

### Additional consent provisions for collection and use of participant data and biological specimens {26b}

Not applicable. No data and biological specimens will be collected for use in ancillary studies.

### Interventions

#### Explanation for the choice of comparators {6b}

Erector spinae plane blocks have been embraced by many anaesthesiologists; however, to the best of our knowledge, there are no clinical effectiveness trial comparing infusion techniques of programmed intermittent bolus vs standard continuous infusion for minimal invasive thoracic surgery in terms of patient centred outcomes and therefore this clinical trial is warranted.

#### Intervention description {11a}

Eligible study participants will receive an ultrasound-guided ESP block post induction of general anaesthesia and prior to commencement of surgery. Blocks will be performed under full asepsis with patients in the lateral decubitus position. Initial bolus of the ESP block will be the same in all patients: Twenty millilitres of 0.25% levobupivacaine will be injected at a level corresponding to the mid-point of the range of surgical dermatomes likely to be affected by the surgery. After administration of the bolus dose, an epidural catheter will be advanced 3–5 cm into the erector spinae space. Typically, ESP block and catheter insertion will be administered at T4 level. The ESP block will be performed as follows.

First, the approximate midpoint of the intended surgical incision will be identified. The ultrasound transducer (SonoSite HFL 50x, SonoSite Inc.) will then be placed in a longitudinal orientation approximately to 2–3 cm lateral to the midline, to identify the hyperechoic line of the transverse process with its associated acoustic shadow. After identification of trapezius, rhomboid major and erector spinae muscle groups superficial to the transverse process, an 18G Tuohy epidural needle (Ultraplex; B. Braun, Hessen, Germany) will be advanced in a cranio-caudal direction. The needle tip will be advanced until it is in the interfascial plane deep to the erector spinae muscle group and superficial to the transverse process. Once in position, 20 ml 0.25% levobupivacaine will be injected under ultrasound guidance. Correct needle tip position will be confirmed by the presence of linear spread between the transverse process and the erector spinae muscle group. After administration of a bolus dose, a 20G polyether epidural catheter (Ultraplex 360 cannula; B. Braun, Hessen, Germany; 50e80 mm) will be advanced through the Tuohy needle and into the ESP space. The catheter will be adjusted so that approximately 3–5 cm of the catheter will be in the ESP space. The catheter will then be secured in this position. Because patients will be under general anaesthesia during the block performance, no formal dermatomal sensory testing of block efficacy will be performed at this time. Surgery will begin once the block is completed. There will be no further intervention to the routine conduct of surgery and anaesthesia after this point. Blocks will be performed by anaesthesiologist with subspeciality training in regional anaesthesia. Two hours post administration of the ESP bolus dose, the ESP catheter will be connected and commenced with either the PIB or CI regimen (randomised process).

The PIB patients will receive levobupivacaine 0.125% programmed bolus 20 ml 2 hourly. The CI group will receive continuous infusion levobupivacaine 0.125% at 10 ml.h^−1^. Therefore, both arms of the study will receive 25mg levobupivacaine every 2 h.

#### Criteria for discontinuing or modifying allocated interventions {11b}

Criteria for discontinuing study protocol are as follows:Unexpected regional anaesthesia complicationSuspected or confirm diagnosis of local anaesthesia toxicityUnexpected postoperative admission to intensive care unitInability to insert ESP catheterPatient request to be withdrawn from studyClinical concern of patient’s care from surgical, anaesthesia, or research team

#### Strategies to improve adherence to interventions {11c}

The study flow chart (Fig. 1) and analgesia and anti-emetic protocol (Fig. 2) will be made available in the operating theatre and post anaesthesia care unit (PACU). These protocols will be available to anaesthesiologist and surgeons performing the intervention and data collectors to ensure protocol adherence.

**Fig. 2 Fig2:**
[figure not shown]
Analgesia and anti-emetic protocol

#### Relevant concomitant care permitted or prohibited during the trial {11d}

All study participants will undergo general anaesthesia (GA) as per standard care for MITS. Induction of GA will be conducted or supervised by a consultant anaesthesiologist. Induction of GA will be achieved intravenous administration of fentanyl, propofol, and a neuromuscular blockade agent at the discretion of the anaesthesiologist.

Airway management will be at the discretion of the treating anaesthesiologist. Ventilation strategy, choice of intraoperative monitoring, and vascular access will also be at the discretion of the treating anaesthesiologist. The haemodynamic goal will be to maintain systolic blood pressure within 20% of the patient’s baseline. Persistent intraoperative elevations above this point will trigger the administration of intravenous opioids. The dosage and timing of this will be at the discretion of the treating anaesthesiologist. Intravenous (IV) paracetamol and an IV non-steroidal anti-inflammatory drug will be delivered intraoperatively where clinically appropriate and at the discretion of the treating anaesthesiologist.

A concomitant care plan for perioperative analgesia and anti-emetics will be standardised for the pre-surgical, intra-operative, PACU, and post-operative period. This is outlined in Fig. 2.

#### Provisions for post-trial care {30}

Study participants are covered by indemnity for negligent harm, through the standard HSE (Health Service Executive) indemnity arrangements. If any complications arise directly from either intervention, the participant will receive standard post-operative management which may include management from the surgical team, pain medicine department, and multidisciplinary team. Additionally, all investigators will be employees of the respective hospitals and will be covered by the HSE clinical indemnity scheme.

### Outcomes {12}

#### Primary outcome measures

Quality of Recovery (QoR-15) score of the programmed intermittent bolus group vs the continuous infusion group at 24 h postoperative [time frame: 24 h postoperative] [14, 15].QoR-15 is a 15-parameter questionnaire which has been validated as an optimal tool to measure overall patient recovery after surgery including postoperative pain. Participants will complete this questionnaire at 24 h after their surgery. Each question will be scored from 0 ‘none of the time’ to 10 ‘all the time’ except for questions 11–15, which will be score inverted: 10 ‘none of the time’ to 0 ‘all the time.’ The total QoR-15 score ranges between 0 and 150, where 150 illustrates that the patient has had an excellent recovery.

#### Secondary outcome measures

Quality of Recovery (QoR-15) score of the programmed intermittent bolus group vs the continuous infusion group at 48 h postoperative [time frame: 48 h postoperative] [14, 15].Pulmonary function assessment [time frame: pre-operatively day 0, post-operative day 1, and post-operative day 2]Pulmonary function assessment will be undertaken pre-operatively (day 0) before induction of GA and at post-operative day 1 and 2 using bedside incentive spirometry. The average of three maximum inspiration volumes will be measured with the patient in the sitting position. Any change in maximum inspiratory volumes between pre-operative and postoperative days 1 and 2 will be evaluated.Area under the curve (AUC) of Verbal Rating Score (VRS) for pain at rest and on deep inspiration versus time over 48 h [time frame: 60–120 min in PACU, 24 and 48 h post-operative]Verbal Rating scale is measured from 0 to 10, where ‘0’ indicates no pain and ‘10’ indicates severe pain.Time to administration of first postoperative intravenous opioidDuration of time in PACUTotal 24 h and 48 h opioid consumptionTime to first mobilisationDocumentation of adverse eventsThis includes intra-operative haemodynamic changes, post-operative hypotension, nausea and vomiting, pruritis, block failure, and block-related complications.Length of hospital stay [time frame: 1 month]

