#### Sample size {14}

The primary outcome of this study will be the QoR-15 score at 24 h postoperatively. This score rates 15 subjective, patient-reported parameters about their recovery on a scale of 0–10. Therefore, the minimum possible score is 0, and the maximum possible score is 150. The established minimum clinically important difference in QoR-15 is 6.0 [14], and the mean SD of QoR-15 scores after major surgery is in the order of 8–16. Taking an SD of 8, and assuming type I error = 0.05 and type II error = 0.2 (80% power to detect this difference), then *n* = 28 patients will be required in each group. To accommodate for participants who may withdraw from the study, we will aim to recruit *n* = 30 patients to each study arm, i.e. *n* = 60 in total.

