### Statistical methods

#### Statistical methods for primary and secondary outcomes {20a}

The collected raw data will be inspected for any errors. These include but are not limited to, double entry errors, missing data, and data that was incorrectly entered. Data will be recorded in Excel™ (Microsoft, Redmond, WA, USA) and subsequently imported into GraphPad Prism version 9.3.1 (GraphPad, Salt Lake City, UT, USA) for statistical analysis. All data will be stored according to EU Directive 2019 on General Data Protection Regulations. Data will be inspected and tested for normal distribution according to the Shapiro-Wilk test and quantile-quantile (QQ) plot graph as appropriate. Normally distributed data will be compared between study arms using the unpaired *t* test, whereas non-normally distributed data will be compared using Mann-Whitney *U* test. Fisher’s exact test was used for comparing categorical data. All data will be summarised as mean (SD), median (25–75% range), and *n* (%) as appropriate, and *p* value < 0.05 will be considered statistically significant.

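### Change in maximum inspiratory volume is compared between arms with no baseline covariate: valid, but generally less precise than adjusting for the preoperative value already collected

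*Protocol article*

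**What the plan says.** Under the secondary outcome measures, the protocol article sets the measurement times: "Pulmonary function assessment will be undertaken pre-operatively (day 0) before induction of GA and at post-operative day 1 and 2 using bedside incentive spirometry". Each value is the average of three maximal inspirations taken sitting. The quantity of interest follows: "Any change in maximum inspiratory volumes between pre-operative and postoperative days 1 and 2 will be evaluated". It is not said whether change is absolute or a percentage.

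The section on statistical methods for primary and secondary outcomes {20a} chooses the test by distribution: "Normally distributed data will be compared between study arms using the unpaired" t test, "whereas non-normally distributed data will be compared using Mann-Whitney" U test. The threshold is that a p "value < 0.05 will be considered statistically significant". The section names no regression, analysis of covariance or repeated-measures model, and no covariate. The section on additional analyses {20b} says only that there are no subgroup analyses.

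**The concern.** The trial collects a baseline for this outcome but uses it only as something to subtract. Subtraction fixes the baseline coefficient at 1. If the true slope of postoperative on preoperative volume differs from 1, the change score stays correlated with baseline, and that leftover variation widens the confidence interval. In a trial of 60 patients, precision on a secondary outcome is scarce, and here some can be had from data already on the case record form. What is at stake is the width of one interval and the power of one secondary comparison.

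**Working it through.** **The protocol's own figure first.** No calculation is given for inspiratory volume. The only one is for QoR-15: "The established minimum clinically important difference in QoR-15 is 6.0" and "Taking an SD of 8, and assuming type I error = 0.05 and type II error = 0.2 (80% power to detect this difference". With 1:1 allocation and a two-sided test (sidedness is not stated, so two-sided is assumed), n per arm = 2 × (1.960 + 0.842)² × 8² / 6² = 27.9, which rounds up to 28 as stated. The exact t calculation gives 29. The recruitment target is 30 per arm. Nothing below alters this, because the discussion says no preoperative QoR-15 is taken, so there is no baseline to adjust for.

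**Inputs for inspiratory volume.** From the protocol: 30 per arm and one preoperative value. Assumed, because the protocol gives neither: the pre/post correlation r and k, the ratio of postoperative to preoperative SD. Change is taken as an absolute difference. The formulas compare means and do not apply directly to the Mann-Whitney test.

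**Variances, in units of the preoperative variance.**
- Change score: 1 + k² − 2rk, which is 2(1 − r) when k = 1.
- Baseline-adjusted (ANCOVA): k²(1 − r²), which is 1 − r² when k = 1.
- Difference between them: (1 − rk)². It is zero when the slope rk equals 1 and positive otherwise.

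At k = 1 the relative reduction is (1 − r)² / [2(1 − r)] = (1 − r)/2. Estimating one coefficient costs a factor of about 1 + 1/(N − 4) = 1 + 1/56 = 1.018 at N = 60.

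The power columns take an effect that the change-score test would detect with 80% power at 30 per arm. The last column is 30 × 2(1 − r)/(1 − r²), without the covariate cost.

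| r (assumed, k = 1) | Variance reduction | After covariate cost | ANCOVA power | Power after cost | Change-score n per arm to match ANCOVA at 30 |
|---|---|---|---|---|---|
| 0.3 | 35% | 34% | 0.94 | 0.93 | 46 |
| 0.5 | 25% | 24% | 0.90 | 0.89 | 40 |
| 0.7 | 15% | 13% | 0.86 | 0.85 | 35 |
| 0.8 | 10% | 8% | 0.84 | 0.83 | 33 |
| 0.9 | 5% | 3% | 0.82 | 0.81 | 32 |

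**Sensitivity to the SD ratio.** At k = 0.8 the ratio of ANCOVA to change-score variance is 0.57, 0.60, 0.63, 0.64 and 0.61 for r = 0.5, 0.6, 0.7, 0.8 and 0.9, a reduction of 36% to 43%. In the other direction the gain can vanish: at k = 1.25 and r = 0.8 the slope is 1 and both variances are 0.5625. At k = 1 the covariate cost cancels the gain when 1.018 × (1 + r)/2 = 1, at r of about 0.965.

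**Where chance imbalance enters.** At k = 1, 2(1 − r) = (1 − r²) + (1 − r)². The second term is the variance that chance baseline differences add to the change-score comparison. It is exactly what ANCOVA removes, so imbalance and lost precision are one loss.

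**The case against.** Comparing change between randomised arms is a legitimate analysis, and the plan does use the baseline. Patients are "randomly and equally (1:1) allocated into one of two intervention groups", so the change-score comparison is unbiased over repeated randomisations. A reader might infer that the plan biases the result through chance imbalance. The documents do not support that: given a particular imbalance the estimate does shift, but across randomisations this is variance, already counted in the table. This part of the objection stands.

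It can also be said that section 20a is generic, does not mention inspiratory volume, and that covariates are often left to an analysis plan that is not shown. This stands in part. The definition of change is open, and a fuller document might settle it. But 20a is headed for secondary outcomes and names the tests, so the article states an unadjusted comparison and does not leave the method open.

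Third, repeated readings in the same patient one or two days apart may correlate highly, and then little is gained. This stands as a limit on size: at equal SDs the reduction is 10% at r = 0.8 and 5% at r = 0.9, before the covariate cost.

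Finally, a reader might rank this as the main objective secondary outcome, or as better protected from unblinding than QoR-15. The protocol supports neither. Its list sets no hierarchy and puts QoR-15 at 48 h first, and a maximal inspiration also depends on the patient's effort.

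**Conclusion.** The point holds as one of efficiency. As written, the protocol compares change in maximum inspiratory volume with no covariate, which is valid and unbiased but generally less precise than estimating the baseline coefficient. For r between 0.5 and 0.8 and equal SDs, adjustment would cut the variance by 25% to 10% (24% to 8% after the covariate cost), worth about 10 to 3 patients per arm on this outcome. These figures rest on assumed values of r and k and on change being an absolute difference. The gain is larger if the SD shrinks after surgery and disappears as the slope approaches 1. Severity is minor: one secondary outcome is affected, and the primary analysis and the 28 and 30 per arm stand.

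**What to change.** In section 20a, state that maximum inspiratory volume on day 1 and on day 2 will each be compared by linear regression on arm with preoperative volume as covariate. Alternatively, specify one repeated-measures model with arm, day, arm-by-day and preoperative volume. Report adjusted mean differences with 95% CIs. Keep the unadjusted change as a descriptive summary, and say whether it is absolute or a percentage.

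The cost is a change of analysis wording. It needs no new measurements or patients, and should be fixed before the groups are unblinded.
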